**Primary outcomes**			
Dorsiflexion at 3 weeks post-tenotomy	Equal range of dorsiflexion	Degrees of dorsiflexion with 5° increments	Multi-level mixed effects linear regression
Dorsiflexion at 3 months post-tenotomy	Equal range of dorsiflexion	Degrees of dorsiflexion with 5° increments	Multi-level mixed effects linear regression
**Secondary outcomes**			
Pirani score at 3 weeks post-tenotomy	Equal score	Pirani score with 0.5-point increments	Multi-level mixed effects linear regression
Pirani score at 3 months post-tenotomy	Equal score	Pirani score with 0.5-point increments	Multi-level mixed effects linear regression
Minor complications at 3 weeks post-tenotomy	Equal count	Number of minor complications	Multi-level mixed effects logistic regression
Minor complications at 3 months post-tenotomy	Equal count	Number of minor complications	Multi-level mixed effects logistic regression
Major complications at 3 weeks post-tenotomy	Equal count	Number of major complications	Multi-level mixed effects logistic regression
Major complications at 3 months post-tenotomy	Equal count	Number of major complications	Multi-level mixed effects logistic regression
*Complication subgroup analysis*	*Equal count*	*Number of specific type of complications*	Multi-level mixed effects logistic regression

Non-inferiority will be established if the confidence interval for the needle group does not cross the non-inferiority margin. In practice, this means a confidence interval including only values < 4. If the confidence interval includes the value 4, the trial will be determined inconclusive. If the confidence interval only values > 4, the needle tenotomy technique will be considered inferior to the blade technique.

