**Methods:**

We will randomize 244 feet into group A: needle tenotomy or group B: blade tenotomy. Randomization will be done using a block randomization with random block sizes and applying a 1:1 allocation to achieve an intervention and control group of the exact same size. Children will be evaluated at 3 weeks and 3 months post-tenotomy for primary and secondary clinical outcomes. The primary clinical outcome will be the range of dorsiflexion obtained the secondary clinical outcomes will be frequency of minor and major complications and Pirani score. The non-inferiority margin was set at 4°, and thus, the null hypothesis of inferiority of the needle technique will be rejected if the mean difference between both techniques is less than 4°. The statistical analysis will use a multi-level mixed effects linear regression model for the primary outcomes and a multi-level mixed effects logistic regression model for the secondary clinical outcomes. The physician performing the evaluations post-tenotomy will be the only one blinded to group allocation.

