**Fig. 3 Fig3:**
[figure not shown]
Inverse-variance model with random effects to determine mean dorsiflexion rate using blade tenotomy

$$\begin{array}{c}\mathrm{Non}-\mathrm{inferiority \,margin}\\ =\mathrm{ mean \,range \,of\, dorsiflexion \,from\, literature }-\mathrm{ minimally\, acceptable\, range\, of\, post}-\mathrm{operative\, dorsiflexion}\\ = 21.42^\circ - 17.5^\circ \\ = 3.92^\circ \end{array}$$

For practical purposes, a non-inferiority margin of 4° will be applied instead of 3.92.

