#### Sample size and power calculation

Sample sizes are calculated using the WHO sample size determination software [22].

Sample size calculation for primary outcome:Alpha = 5%Power 95%Non-inferiority margin: 4Standard deviation: 9.02

Required sample size = 222 feet (111 in each arm).

Drop-out from clubfoot programs is a common event in LMICs, especially throughout the bracing phase. In literature, drop-out rates of up to 30% have been reported over the total period of bracing which is about 3 years on average [17, 18, 23]. Internal data from the Pehla Qadam clubfoot program shows similar outcome with about 30% drop-out over the entire course of the treatment. We therefore expect during the first year of follow-up to lose about 10% of our patients. We will therefore increase the sample size by 10% to adjust for the expected drop-out.

A total sample size of 244 feet (122 per arm) will be recruited for this trial.

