#### Outcomes

Group A will be compared to group B for the primary and secondary analyses. A multi-level mixed-effects regression model will be used to assess the outcomes. An overview of the different variables to be assessed can be found in Table 1. A linear regression model will be used for the continuous variables and a logistic regression model for the binary variables. If a child received a tenotomy on both feet, these two feet will be clustered, and the analysis must make an adjustment for the lack of independence between measures on these two feet. A mixed-effects model allows for the inclusion of a random subject effect to the regression model, accounting for correlation between pairs of feet on the same child and also assessing the treatment effect from both between-subject differences and within-subject differences. Stata Version 17 (StataCorp, TX, USA) will be used for the analysis. A *p*-value < 0.05 will be considered significant. We will use the one-tailed *p*-value for all our analyses.

**Table 1 Tab1:** Clinical outcomes and proposed statistical analysis

Variable/outcome	Hypothesis	Outcome measure	Method of analysis

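### The primary non-inferiority rule is misstated and inconsistent: the 4° margin is applied to an interval for the needle arm, the contrast is not written out, and the abstract uses no confidence bound

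*Protocol article*

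**What the plan says.** The decision rule, or part of it, appears in four places in the protocol article.

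- **Data analysis and statistical methods, Outcomes, below Table 1.** "Non-inferiority will be established if the confidence interval for the needle group does not cross the non-inferiority margin". The next sentence begins "In practice, this means a confidence interval including only values" and sets the limit at below 4. An interval that includes 4 makes the trial inconclusive. An interval wholly above 4 makes the needle inferior to the blade. No contrast, order of subtraction or confidence level is given here.
- **Same section, opening text.** "Group A will be compared to group B for the primary and secondary analyses", where A is the needle and B the blade. Tests are one-tailed at 0.05.
- **Abstract, Methods.** "the null hypothesis of inferiority of the needle technique will be rejected if the mean difference between both techniques is less than 4" degrees. There is no confidence bound and no sign. The last paragraph of the Discussion also describes non-inferiority as an unsigned mean difference below 4°.
- **Table 1.** The hypothesis listed for dorsiflexion at both visits is "Equal range of dorsiflexion".

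The margin is the pooled blade mean from the literature, 21.42°, less a minimum acceptable 17.5°: "For practical purposes, a non-inferiority margin of 4° will be applied instead of 3.92". The sample size section gives "Alpha = 5%Power 95%Non-inferiority margin: 4Standard deviation: 9.02" and "Required sample size = 222 feet (111 in each arm").

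**The concern.** This rule turns the data into the trial's conclusion, so a reader should not have to infer its parts. Three things are wrong on the page.

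1. **Wrong quantity.** The margin measures a loss relative to blade. It has no meaning against an interval for the needle arm's own mean.
2. **Contrast left to inference.** The last sentence of the rule makes sense only for blade minus needle. The analysis text compares needle with blade, and a regression coefficient for the needle arm would normally carry the opposite sign. An analyst who sets that coefficient against a limit of below 4 would be using the wrong tail.
3. **Two different rules.** The abstract rejects on the mean difference itself; the Methods reject on an interval. The two disagree over a range of results that could plausibly occur.

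The equality hypothesis in Table 1 adds to the confusion, because it does not correspond to a test against a 4° margin.

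**Working it through.** **Inputs.** Margin 4°, SD 9.02, alpha 5%, power 95%, 111 feet per arm (Sample size and power calculation); one-tailed testing at 0.05 (Outcomes); pilot mean 20.2° (Non-inferiority margin determination). Normal approximation, with feet treated as independent, as in the protocol's own calculation.

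**1. Reproduce the sample size.** n per arm = 2 × (z_alpha + z_power)² × SD² / margin².
- One-sided 5%: 2 × (1.645 + 1.645)² × 9.02² / 4² = 110.1, so 111 per arm and 222 in total. This matches.
- One-sided 2.5%: 2 × (1.960 + 1.645)² × 9.02² / 4² gives 133 per arm. This does not match.

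The trial was therefore sized on a one-sided 5% test, which corresponds to the limit of a two-sided 90% interval.

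**2. Standard error of the difference.** 9.02 × √(2/111) = 1.211°. The half-width is 1.645 × 1.211 = 1.99° for a 90% interval and 1.960 × 1.211 = 2.37° for a 95% interval.

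**3. The needle-arm interval read literally.** The standard error of one arm's mean is 9.02 / √111 = 0.856°. Assuming a needle mean equal to the pilot mean of 20.2°, the 95% interval is 20.2 ± 1.68, about 18.5° to 21.9°. It lies wholly above 4, so a needle that works well would be called inferior.

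**4. Chance of declaring non-inferiority, by true needle deficit D (blade minus needle).** Abstract's rule: Φ((4 − D)/1.211). Interval rule: Φ((4 − D)/1.211 − z), with z = 1.645 for the 90% and 1.960 for the 95% interval.

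| True D | Abstract's rule | 90% interval | 95% interval |
|---|---|---|---|
| 0° | 99.95% | 95.1% | 91.0% |
| 4° | 50% | 5.0% | 2.5% |
| 5° | 20.4% | 0.7% | 0.3% |
| 6° | 4.9% | 0.05% | 0.02% |
| 8° | 0.05% | about 0 | about 0 |

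**5. Where the two rules disagree.** The largest observed deficit that passes the interval rule is 4 − 1.99 = 2.0° (90%) or 4 − 2.37 = 1.6° (95%). Observed deficits of about 2.0° to 4.0° are non-inferior by the abstract and inconclusive by the Methods with a 90% interval. At a true 3° deficit this happens with probability Φ((4 − 3)/1.211) − Φ((2.01 − 3)/1.211) = 0.80 − 0.21, about 59%. Observed deficits between 1.6° and 2.0° change verdict with the confidence level.

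**6. Sign reversed.** If needle minus blade were set against a limit of below 4, the chance of passing would be Φ((4 + D)/1.211 − z), which is practically 100% for every D from 4° to 10°.

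**The case against.** The strongest reply is that the Methods rule, read as a whole, is sound. Its last sentence ties values above 4 to an inferior needle, which fixes the sign as blade minus needle. The margin derivation agrees, since it subtracts a minimum acceptable value from the blade mean. The interval for the needle group is then a drafting slip: nobody would set an interval around 20° against 4, because non-inferiority could never be reached. The abstract condenses a rule that the Methods give in full, and the Discussion sentence can be read as describing the true difference. The confidence level can be recovered from the one-tailed 0.05 and the 222 feet, and is often left to an analysis plan. Table 1's column is headed as a hypothesis, not a null, and the abstract names inferiority as the null.

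Much of this stands. A reader might infer that no direction exists and that any deficit, however large, would pass. The documents do not support that: it needs a sign that the rule's own last sentence contradicts. A reader might also infer that Table 1 sets up a null of equality as a second decision rule; the column heading does not say so. The missing confidence level would not be a finding on its own.

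The reply does not remove the conflict. The protocol states the rule itself and names the wrong quantity in doing so. The abstract gives a rejection criterion that is not a shortened form of an interval rule. The sign has to be inferred against text that compares needle with blade.

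**Conclusion.** The point holds as an error of statement and consistency in the primary decision rule. The intended rule can be reconstructed and is valid: with blade minus needle, the false-declaration rate at a true 4° deficit is 5.0% with a 90% interval or 2.5% with a 95% interval. Taken as the rule, the abstract's wording raises that rate to 50%, with 20% at 5°. The excess is concentrated near the margin and is negligible at 8°. The literal needle-arm interval errs the other way and would condemn a good needle. A grossly inferior needle would pass only if the sign were reversed.

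The figures assume SD 9.02, 111 evaluable feet per arm, a normal approximation and independent feet. Correlation between feet of the same child would alter the standard error but not the conflict between the rules. The sample size calculation is not at fault here.

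**What to change.** State one rule and use it throughout, before any comparison of the arms is seen:

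- D = mean dorsiflexion at 3 months, blade minus needle, from the mixed model.
- H0: D ≥ 4°; H1: D < 4°.
- Non-inferior if the upper limit of the two-sided 90% confidence interval for D (one-sided 5%) is below 4°; inconclusive if the interval contains 4°; inferior if the lower limit exceeds 4°.

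Replace the paragraph below Table 1 with this text, add the confidence bound and the sign to the abstract and the Discussion, and put the non-inferiority hypothesis in the Table 1 row for dorsiflexion at 3 months. Bring the 3-week row into line, so that equality is not left standing beside a margin-based test.

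With the 90% interval the cost is wording only, and the 222 evaluable feet stand. If the team prefers a 95% interval, it should restate power as about 91%, or plan 133 evaluable feet per arm to keep 95%.

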#### Analysis population and missing data

We will test for non-inferiority using the “intention-to-treat” approach. All participants will be assessed as part of the group they were randomized to. Children who were randomized to group A: needle tenotomy and received a blade tenotomy instead because of a decision made at the treating physician’s discretion are excluded from the trial. Cross-overs from the blade to the needle tenotomy group are not a possibility in our trial, given that the blade tenotomy is the gold standard and the “experimental” needle tenotomy is not performed based on parents’ request or physician’s preference. Therefore, there is no valid reason to assess the data in a “per-protocol” fashion.

As stated earlier, given the follow-up duration of 1 year, we expect a drop-out rate of about 10%, and the sample size will be adjusted for this expected loss-to-follow-up. Previous research shows that drop-out is predominantly related to a mix of socio-economic and contextual factors and much less related to the level of correction of the deformity or the satisfaction of the parents [18, 23]. Missing data is therefore considered to be missing at random (MAR) and no dummy variable creation or imputation will be done as the mixed effects regression models provide valid estimates under MAR.

Children who missed out on both follow-up consultations and for whom we were not able to schedule a follow-up consultation within 6 months of the tenotomy will be excluded from the trial.

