#### Modification in allocated interventions

Cross-over between groups is not allowed in the trial. If a change of intervention is deemed necessary by the treating physician after group allocation, the patient will be removed from the trial and receive the appropriate care deemed necessary by their treating physician.

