#### Concomitant care

All patients are allowed to receive concomitant care as deemed necessary by their treating physician. In case concomitant care requires the removal of the cast during the first 3 weeks after tenotomy, and no new cast can be applied within 24 h of removal, the patient will be removed from the trial.

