### Blinding

#### Blinding/masking

Assessment of primary and secondary outcomes will be assessed by clinical officer on duty at the Pehla Qadam clubfoot clinic and will be blinded to group allocation. The medical officer sees all children attending the clinic and will not be aware if the child is enrolled in the trial and in which group his/her foot/feet are randomized and if the child received an Achilles tendon tenotomy or not. The program coordinator will extract the necessary data for the trial from the Pehla Qadam logbooks after every clinic day as to protect the blinding at the assessor level during clinic.

Given the nature of the intervention, the physician doing the tenotomy cannot be blinded to group allocation. Parents/caregivers can be informed about group allocation if they wish to know, at the time the tenotomy is performed.

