#### Emergency unblinding

Emergency unblinding is not applicable in this trial. The medical officer assessing the patient’s foot/feet at 3 weeks and 3 months post-tenotomy is the only provider blinded to group allocation in this trial. If he/she believes the child requires additional assessment, because of inadequate progression during treatment, he/she can refer the child to the treating orthopedic surgeon for further assessment. The treating orthopedic surgeon is aware of the group allocation and will do all necessary assessments and will put the child’s health before the trial. This may include unenrolling the child from the trial, if necessary. The medical officer on duty will remain blinded to the group allocation for this respective child.

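### The analysis labelled intention-to-treat drops children converted from needle to blade, so it is not the randomised comparison; the size and direction of any bias cannot be determined from the protocol

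*Protocol article*

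**What the plan says.** All references are to the protocol article.

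- Analysis population and missing data names the approach intention-to-treat and states: "All participants will be assessed as part of the group they were randomized to".
- The next sentence begins "Children who were randomized to group A: needle tenotomy and received a blade tenotomy instead because of a decision made at the treating" physician's discretion, and says that these children are excluded from the trial.
- The same section rules out the reverse: "Cross-overs from the blade to the needle tenotomy group are not a possibility in our trial". From this it concludes that "there is no valid reason to assess the data in a “per-protocol” fashion".
- Modification in allocated interventions has a general rule, worded for either arm: "If a change of intervention is deemed necessary by the treating physician after group allocation, the patient will be removed from the trial".
- Concomitant care removes a child whose cast has to come off in the first 3 weeks for other care, if "no new cast can be applied within 24 h of removal, the patient will be removed from the trial".
- Emergency unblinding lets the blinded medical officer refer a child for inadequate progression to the treating surgeon, who knows the allocation. Of the surgeon's options it says: "This may include unenrolling the child from the trial, if necessary".
- Blinding/masking confirms that "the physician doing the tenotomy cannot be blinded to group allocation".
- Missing data are taken to be missing at random because drop-out is mainly socio-economic and contextual.

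**The concern.** Intention-to-treat keeps each participant in the allocated arm whatever treatment was received. A rule that removes participants after randomisation because of the treatment they received is the opposite, so two adjacent sentences of the plan cannot both be followed.

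Three features make this more than a labelling slip. First, the protocol's own wording confines the conversion exclusion to the needle arm. Second, the decision to convert lies with a physician who knows the allocation. Third, no other analysis set is planned in which these feet would reappear, because a per-protocol analysis is rejected as well.

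At stake are the protection that randomisation gives to the primary comparison and the visibility of conversions. The Background and Rationale aim the technique at non-surgeon providers, so how often a needle tenotomy has to become a blade tenotomy is itself a result that readers need.

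The removals under Concomitant care and Emergency unblinding apply to both arms, but they too take children out after randomisation on clinical judgement. The missing-at-random argument concerns families who stop attending for socio-economic reasons. It does not cover removals decided by a clinician.

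**Working it through.** **Reproducing the plan's figure.** Sample size and power calculation gives alpha 5%, power 95%, margin 4° and SD 9.02. Data analysis and statistical methods says that p-values are one-tailed.

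n per arm = 2 × [9.02 × (1.645 + 1.645) / 4]² = 110.06, rounded up to 111, so 222 feet. 222 × 1.10 = 244.2, so 244. Both stated figures reproduce.

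**Effect on precision.** With 10% drop-out, 244 × 0.9 / 2 = 109.8 feet per arm remain and power is 95.0%. Losing a further 5% or 10% of needle feet gives 94.5% or 94.0%. Loss of power is therefore minor; selection is the issue.

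**Effect on the error rate.** The documents give neither the converted fraction c nor the outcomes of converted feet, so both are assumptions. Let f be the number of degrees by which converted feet fall below retained needle feet. Set the true blade-minus-needle difference over all randomised feet at 4°, where non-inferiority should be concluded 5% of the time. Then:

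- difference after exclusion = 4 − c × f
- SE = 9.02 × √[1/(111(1 − c)) + 1/111]
- false non-inferiority rate = Φ[(4 − difference after exclusion)/SE − 1.645] = Φ(c × f/SE − 1.645)

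| c | f | Difference after exclusion | SE | False non-inferiority |
|---|---|---|---|---|
| 5% | −5° | 4.25° | 1.227 | 3.2% |
| 5% | 0° | 4.00° | 1.227 | 5.0% |
| 5% | 5° | 3.75° | 1.227 | 7.5% |
| 5% | 10° | 3.50° | 1.227 | 10.8% |
| 10% | −5° | 4.50° | 1.244 | 2.0% |
| 10% | 5° | 3.50° | 1.244 | 10.7% |
| 10% | 10° | 3.00° | 1.244 | 20.0% |
| 2% | 10° | 3.80° | 1.217 | 6.9% |

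A negative f means that converted feet did better than retained needle feet, and the error rate then falls below 5%.

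**If the blade rescues difficult feet.** Suppose the feet that would be converted are d degrees worse than other feet in both arms, and that after conversion they reach the result a blade would have given them. With the all-randomised difference still at 4°, the difference after exclusion is 4/(1 − c) − c × d. At c = 5%, d = 0 gives 4.21° and 3.5%; d = 5 gives 3.96° and 5.3%; d = 10 gives 3.71° and 7.9%. Exclusion favours the needle only when d exceeds 4/(1 − c), which is about 4.2° here.

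All figures use a normal approximation and treat feet as independent. Clustering of two feet in one child is ignored.

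**The case against.** The strongest objection concerns direction. A converted foot received the comparator. If it then reaches the blade mean, keeping it in the needle arm pulls the arms together, and dropping it is the stricter test. Take a true technique deficit of 4° and SE = 9.02 × √(2/111) = 1.211. Retaining 5% of needle feet at the blade mean gives a difference of 4 × 0.95 = 3.8° and a false non-inferiority rate of Φ(0.2/1.211 − 1.645), about 7%. At 10% the difference is 3.6° and the rate about 9%. With exclusion it would be 5%. This stands: it rules out any statement that the exclusion must favour the needle, and it is why a per-protocol analysis is needed next to the randomised one.

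Two further limits also stand.

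- A reader might infer that every blade foot stays in. The documents do not say so. The removals under Modification in allocated interventions, Concomitant care and Emergency unblinding are worded for either arm; only needle-to-blade conversion is confined to one.
- A reader might infer that converted feet are failed needle attempts. The text speaks only of a physician's decision after allocation, which could precede any attempt. Failures found later are partly covered, since Harms and adverse events monitors repeat tenotomy after 3 weeks for incomplete sectioning. Conversion itself is not on that list.

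None of this reconciles the intention-to-treat label with the exclusion.

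**Conclusion.** The point holds as an internal contradiction with consequences for the primary analysis. The set described is not intention-to-treat, one of its exclusions can occur in the needle arm only and is decided by an unblinded physician, and no planned analysis brings the excluded feet back.

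It is tempting to go further and say that the exclusion biases the trial toward non-inferiority. The documents do not support that, because they give neither a conversion rate nor outcomes of converted feet. Under the stated assumptions with 5% converted, the false non-inferiority rate runs from about 3% (converted feet 5° better than retained needle feet) through 5% (no difference) to about 11% (10° worse). The 20% figure needs both 10% converted and a 10° deficit, which is more than one SD. These are illustrations of sensitivity, not estimates for this trial.

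**What to change.** 1. In Analysis population and missing data, Modification in allocated interventions, Concomitant care and Emergency unblinding, replace exclusion, removal or unenrolment with a statement that the foot stays in data collection and is analysed in its allocated arm, unless consent is withdrawn. This concerns follow-up and analysis status only; treatment remains the physician's decision.
2. Report conversions by arm and reason, with any complications that prompted them.
3. Delete the statement that a per-protocol analysis has no valid reason. Add a per-protocol analysis that excludes converted feet, and require it and the all-randomised analysis to be read together before non-inferiority is claimed.
4. Optionally, add a sensitivity analysis that counts conversions as needle failures.

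The cost is an amendment of wording and a small amount of extra analysis. Patient timeline and Data collection say that visits and outcomes are those of routine clinic follow-up, so no extra visits are needed. The target of 244 feet does not change.

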### Trial design

This trial is designed as a randomized, controlled, single-blinded, single-center non-inferiority trial with two parallel groups and a primary endpoint of achieved dorsiflexion at 3 months after tenotomy. Randomization will be performed as block randomization with a 1:1 allocation.

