### Outcomes

Patients will be followed as per the standard follow-up schedule at the Pehla Qadam clubfoot clinic. Patients will be evaluated at 3 weeks and at 3 months post-tenotomy during regular follow-up consultations. The dorsiflexion range at 3 months post-tenotomy is considered the primary outcome. These measurement points were chosen as they coincide with the standard follow-up appointments established at the Pehla Qadam clubfoot clinic. Given that long-term follow-up is challenging in low-resource settings, the primary outcome measure was the first follow-up visit after cast removal, i.e., 3 months post-tenotomy to minimize drop-out from the trial.

The primary outcome measure is as follows: range of dorsiflexion will be registered at both follow-up visits.

The secondary outcome measures are as follows: complications including neurovascular damage in the heel region, skin, and wound problems or infections will be recorded at both follow-up visits. Neurovascular damage, an infection requiring antibiotic treatment or any other type of complication that requires the consultation of another medical specialty, will be considered a major complication. Scar hypertrophy, local edema, or erythema will be considered minor complications.

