#### Adherence to treatment in trial participants

Adherence to casting and brace wearing after tenotomy is a paramount to the overall success of the Ponseti treatment [1]. All patients at the Pehla Qadam clubfoot clinic receive counseling about the importance of adherence to the prescribed treatment. Patients in the trial will not receive any additional interventions to increase adherence beyond what is already offered as part of the standard treatment regimen.

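### The plan rules out a per-protocol analysis on instrument switching alone, and its only analysis set is not a true intention-to-treat set

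*Protocol article*

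**What the plan says.** Under Analysis population and missing data, the protocol article names intention-to-treat as the approach for the non-inferiority test and says that every participant is analysed in the arm of randomisation. The same paragraph excludes children allocated to the needle who received a blade at the physician's discretion, and states that a switch from blade to needle cannot happen. From these two statements it concludes that "there is no valid reason to assess the data in a" per-protocol way.

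Other sections bear on this:

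- Modification in allocated interventions removes from the trial any patient whose intervention is changed after allocation.
- Concomitant care removes a patient whose cast must come off in the first 3 weeks for other care and cannot be replaced within 24 h.
- Emergency unblinding lets the treating surgeon, who knows the allocation, unenrol a child.
- Adherence to treatment in trial participants says: "Adherence to casting and brace wearing after tenotomy is a paramount to the overall success of the Ponseti treatment". It plans nothing beyond usual counselling.
- Auditing and data monitoring has enrolment criteria checked, without saying how a foot that fails the check is analysed.
- Outcomes fixes the main reading: "The dorsiflexion range at 3 months post-tenotomy is considered the primary outcome". The cast comes off at 3 weeks, so this reading falls about 10 weeks later.
- The only exclusion linked to timing is for children who missed both visits and could not be seen within 6 months.

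**The concern.** The conclusion is wider than its premise. Instrument switching is one kind of protocol deviation. A foot may also be read well before or after 3 months, be found ineligible, lose its cast for a reason that the concomitant-care rule does not cover, or be poorly braced. The argument in the article addresses none of these.

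The direction matters because this is a non-inferiority trial. In a superiority trial, a deviation that pulls the arms together works against the new treatment. Here it moves the confidence interval away from the 4° margin and makes it easier to declare a worse needle non-inferior. With one analysis set, nothing would show that this had happened.

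The set is also not what its name says. Dropping needle feet converted to blade is an exclusion after randomisation, it affects one arm only, and it contradicts the statement that everyone is analysed as randomised. If the converted feet are the difficult ones, leaving them out may also favour the needle. The plan therefore has neither a full randomised set nor a defined per-protocol set.

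**Working it through.** **Inputs from the protocol article.** Margin 4°, SD 9.02°, alpha 5%, power 95% (Sample size and power calculation); one-sided testing, "We will use the one-tailed" p-value (Data analysis, Outcomes); 1:1 allocation, "Randomization will be performed as block randomization with a 1:1 allocation" (Trial design). The share of feet with deviations is not given, so it is an assumption throughout. Feet are treated as independent, as the article's own calculation appears to do.

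**1. The plan's own figure.** n per arm = 2 × SD² × (z₀.₉₅ + z₀.₉₅)² / margin² = 2 × 9.02² × (1.645 + 1.645)² / 4² ≈ 110.1, rounded up to 111. This matches "Required sample size = 222 feet (111 in each arm"). One-sided 5% is therefore the level in use.

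**2. Standard error.** SE = 9.02 × √(2/111) = 1.21°.

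**3. Dilution.** Let D be the true deficit of the needle in feet treated as planned, and f the share of feet in both arms that carry no technique difference. The expected observed deficit is (1 − f) × D, and

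P(declare non-inferiority) = Φ[(4 − (1 − f)D)/1.21 − 1.645].

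With D = 4°:

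| f (assumed) | Observed deficit | P(declare non-inferiority) |
|---|---|---|
| 0% | 4.0° | 5.0% |
| 5% | 3.8° | 7.0% |
| 10% | 3.6° | 9.4% |
| 20% | 3.2° | about 16% |
| 30% | 2.8° | 25.7% |

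With D = 5°, f = 0, 10, 20 and 30% give 0.7, 2.0, 5.0 and 10.9%. False here means relative to the effect in feet treated as planned.

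**4. Deviations that do not dilute.** If 20% of feet in each arm lose 10°, the difference is unchanged and the SD becomes √(9.02² + 0.2 × 0.8 × 10²) = 9.87°. The error at a 4° deficit stays at 5%, and power at zero difference falls from about 95% to about 92%.

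**5. Dropping converted needle feet.** If a share x of needle feet is dropped and these would have read L degrees lower than the rest, the needle mean is overstated by x × L. With x = 5% and L = 10° (both assumed), the bias is 0.5° and the error is Φ(0.5/1.21 − 1.645) = 10.9%. If the dropped feet read like the rest, there is no bias.

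**6. Cost of a per-protocol set.** With 20% of feet removed, about 88 per arm remain. SE = 9.02 × √(2/88) = 1.36°, and power at zero difference is Φ(4/1.36 − 1.645) = 90%. With 10% removed (99 per arm) it is 93%.

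**The case against.** The strongest reply is that tenotomy is a single act whose effect is not withdrawn when a brace is left off. If poor bracing lowers dorsiflexion equally in both arms, the difference survives, as step 4 shows. For late readings, the Discussion gives the premise that the range no longer changes once the tendon has healed at 3 months. Both points stand in part: dilution is possible, not established. The premise does not cover early readings, however, and the same section says that the influence of walking on the range is unknown.

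A reader might infer more than the documents support:

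- *That the plan says cross-overs cannot occur.* It says so only of blade to needle. The reverse is foreseen and excluded.
- *That every foot losing its cast early stays in the analysis.* The concomitant-care rule removes some of them.
- *That feet found ineligible are kept.* The article does not say.
- *That the drop-out statement, "Drop-out from clubfoot programs is a common event in LMICs, especially throughout the bracing phase", shows many deviating feet.* It concerns children who leave. A child gone before 3 months has no primary reading and cannot dilute the 3-month difference. The allowance made for this, "We will therefore increase the sample size by 10% to adjust for the expected drop-out", concerns numbers and not adherence.
- *That the error rates in step 3 are forecasts.* They assume shares of feet with exactly zero technique difference.

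A further fair objection is that the planned set is already near per-protocol on instrument and partly on cast. That is correct. It is why adding a narrower set alone would not be enough: both sets would omit the converted needle feet, and their agreement could falsely reassure.

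**Conclusion.** The point holds in limited form. The article states a decision and a reason, so this is not a detail left to a fuller document, and the reason does not support the decision. Deviations other than switching can occur, and those that shrink the arm difference favour the needle. The size is unknown. As illustration only, at a true 4° deficit the error goes from 5% to about 9% with 10% of feet diluted and about 16% with 20%; it stays at 5% if deviations affect both arms equally.

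Separately, and without any assumption, the set called intention-to-treat contradicts its own definition by dropping converted needle feet. How far this favours the needle depends on how many feet are converted and how they fare, which the documents do not give. Both points merit a change to the analysis section before allocation is joined to the outcome data.

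**What to change.** 1. Delete the sentence that denies a reason for a per-protocol analysis.
2. Analyse all randomised feet with outcome data in their allocated arm, including converted feet. Bring the removal rules in Modification in allocated interventions, Concomitant care and Emergency unblinding into line with this, so that removal from study procedures does not mean removal from the analysis. How children are treated is not affected.
3. Add a supportive per-protocol analysis with the same mixed model and 4° margin, in feet that were eligible, had the allocated instrument, had no cast deviation, and were read within a 3-month window fixed before unmasking. Use brace adherence as a criterion only if the clinic already records it; the article does not show that it does.
4. Report both results side by side, with the number of converted feet. Call non-inferiority robust only if the confidence interval lies below 4° in both.

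The two sets complement each other. A converted foot in the full set carries a reading obtained after a blade, which can itself pull the arms together, while the per-protocol set leaves that foot out.

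The cost is revised wording and one more model run. Follow-up readings are part of standard clinic care, so many feet now removed should have one; data destroyed after withdrawal of consent cannot be used. The supportive set has fewer feet and a wider interval (power about 90% at zero difference if 20% are removed), and it is selected after randomisation, so it should stay supportive.
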